This AI system has been trained and internally validated on a large-scale fundus image dataset from Chinese PLA General Hospital, achieving a mean area under the receiver operating characteristic curve (AUC) of 0.941 for optic disc segmentation, 0.874 for optic cup segmentation, and 0.893, 0.901, 0.969, and 0.892 for the classification of the four aforementioned lesions, respectively (18). It has undergone independent external dataset validation and multicenter prospective clinical performance evaluation, with both algorithmic stability and generalizability systematically assessed. Within our screening workflow, all fundus photographs will first be independently interpreted by ophthalmologists at the level of attending physician or higher, while simultaneously undergoing automated image interpretation and risk stratification by the AI system. Then, the human and AI interpretations will be compared. In cases of disagreement, the images will be referred to a glaucoma specialist for final adjudication, and the specialist’s judgment will serve as the reference standard. This forms a standardized screening pattern combining AI-assisted initial screening with physician review for final confirmation.

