All participants who enter the Tier 3 screening stage will undergo further examinations for definitive diagnosis, including standard automated perimetry for visual field testing, optical coherence tomography (OCT) imaging of retinal nerve fiber layer (RNFL) thickness, and gonioscopy to distinguish open-angle from angle-closure glaucoma. The final diagnosis will be made independently by two glaucoma specialists following a comprehensive review of all clinical data, with reference to internationally accepted diagnostic criteria for glaucoma, namely the presence of characteristic glaucomatous optic neuropathy with corresponding visual field defects, after excluding other ocular or neurological conditions that may cause optic neuropathy. Any diagnostic disagreement between the two specialists will be resolved by a third senior glaucoma expert who will make a final determination. To correct for verification bias, a random sample of 10% of participants who are screen-negative will also be recalled to undergo the same reference standard examination. Sensitivity and specificity of the two screening strategies will be calculated based on all screen-positive participants and the randomly selected screen-negative subset, with appropriate weighting to account for the sampling fraction.

The study is scheduled to begin patient enrollment in October 2025, with follow-up and final data collection expected to be completed in December 2032.

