Secondary outcome measures include comparative analyses of the cost-effectiveness of different screening strategies and the diagnostic accuracy of physician-based versus AI-assisted image interpretation in fundus photography for screening glaucoma. The comparison of diagnostic accuracy will be evaluated at the per-participant level and will include sensitivity and specificity, as well as AUC for each interpretation method.

The cost-effectiveness analysis will be conducted from a societal perspective to comprehensively evaluate the resources consumed and health outcomes generated by different screening strategies. The primary economic outcome is the incremental cost-effectiveness ratio (ICER), expressed as the incremental cost per additional glaucoma case detected (based on observed data within the study period), and the incremental cost per quality-adjusted life year (QALY) gained (based on long-term model extrapolation). Cost components will encompass screening-related expenses, including personnel, equipment, consumables, site costs, and AI-assisted interpretation fees; diagnostic confirmation costs following referral, such as OCT and automated perimetry; subsequent treatment and follow-up costs; and direct non-medical and indirect costs, including transportation expenses and productivity losses incurred by patients and their families. Health utility values will be measured prospectively among diagnosed patients during follow-up using the EQ-5D-5L instrument and converted to utility weights using the Chinese value set. Costs and effects within the study period will be obtained through actual data collection, whereas long-term outcomes will be evaluated using a Markov state-transition model simulating the natural history of glaucoma and the long-term trajectory following screening intervention. The model will employ a cycle length of 1 year and a lifetime horizon, and future costs and health outcomes will be discounted to present value at an annual rate of 3%. Uncertainty in the incremental analysis will be assessed through one-way sensitivity analyses and probabilistic sensitivity analysis, and cost-effectiveness acceptability curves will be generated to illustrate the probability that the tiered screening strategy is cost-effective across a range of willingness-to-pay thresholds.

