### Quality control, data management and supervision

2.7

The quality control and supervision of this study involve the following points:

(1) Prior to study initiation, standardized operating procedures (SOPs) are formulated for visual acuity testing, IOP measurement, fundus photography, and ocular optical biometry at community-based physical examination centers. All examiners will undergo standardized training on these protocols and are required to demonstrate competencies through formal assessment before being permitted to participate in the study.(2) The original data of examinations including visual acuity, IOP, and optical biometry will be retained for storage in the disease-specific database of the cohort study office, West China Hospital of Sichuan University. At least two researchers complete the form entry and checking work.(3) Fundus photographs are initially interpreted by experienced physicians holding a rank of attending physician or higher. Then, these assessments are compared with AI-based image analyses. Regarding discrepancy between the human and AI interpretations, the images will be referred to a glaucoma specialist for arbitration, with the expert’s judgment serving as the gold standard.(4) Automated perimetry and RNFL thickness measurements are served as definitive diagnostic tests, with all results being evaluated and confirmed by a glaucoma specialist whose judgment constitutes the gold standard.(5) All screening instruments and follow-up questionnaires would be reviewed by dedicated personnel. If there are incomplete filling out of forms or questionable responses, immediate follow-up contacts will be initiated for verification.(6) A central database is planned to be established and all data can be uploaded to the central database through the researchers in a timely manner, or directly through the inspection equipment via Internet.(7) The study involves a prolonged follow-up period, during which participant attrition is anticipated. The initial sample size calculation has taken an estimated loss-to-follow-up rate (20%) into consideration by expanding sample size. Furthermore, multiple strategies will be employed to enhance participant compliance, including simplifying questionnaire content to reduce response burden, shortening examination duration, and providing subsidies (financial support provided to cover or offset costs associated with the screening process, such as transportation expenses) as necessary. Additionally, active reattempts are made to contact participants lost to follow-up to determine reasons for withdrawal and minimize attrition wherever possible.

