Additionally, the cost-effectiveness analysis will adopt ICER as the economic evaluation measure, with estimated CIs using nonparametric bootstrapping. The sensitivity, specificity, and AUC of physician-based versus AI-assisted image interpretation will be calculated and compared, and differences in AUC will be assessed by the DeLong test or bootstrapping.

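### The only reference standard tied to physician-versus-AI image reading covers discordant images alone, and the Tier 3 diagnosis with its weighted 10% recall is not linked to that comparison

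*Protocol article*

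**What the plan says.** **Reading workflow (2.2 Study design).** Both readers see every image: "all fundus photographs will first be independently interpreted by ophthalmologists at the level of attending physician or higher", with the AI reading in parallel. The two readings are compared. If they differ, "the images will be referred to a glaucoma specialist for final adjudication, and the specialist’s judgment will serve as the reference standard".

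**Quality control (2.7, item 3).** The same rule appears again: for discrepant readings, "the images will be referred to a glaucoma specialist for arbitration, with the expert’s judgment serving as the gold standard". Item 4 of that list names a separate gold standard for the definitive tests (perimetry and RNFL thickness, confirmed by a glaucoma specialist).

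**The outcome (2.6 and 2.9).** The secondary outcomes include "the diagnostic accuracy of physician-based versus AI-assisted image interpretation in fundus photography for screening glaucoma". Section 2.6 sets the analysis per participant, and section 2.9 says "The sensitivity, specificity, and AUC of physician-based versus AI-assisted image interpretation will be calculated and compared". Neither section states what the readings are scored against.

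**The other reference (2.2).** Everyone entering Tier 3 has perimetry, OCT and gonioscopy, and two glaucoma specialists diagnose independently. A random 10% of screen-negatives is recalled for the same examination. The use given for these data is: "Sensitivity and specificity of the two screening strategies will be calculated based on all screen-positive participants and the randomly selected screen-negative subset", with weighting for the sampling fraction. Reader accuracy is not mentioned there.

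**The concern.** Reader accuracy is the direct evidence for secondary objective 2, the evaluation of the AI tools. The protocol labels one thing as the standard for image reading, twice, and that thing exists only where the readers differ. Concordant images, normally the great majority, get no independent status from it.

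Two analyses follow naturally from such a rule, and neither is sound. If the shared call is accepted as true, a case that both readers miss becomes a true negative, and a false alarm that both raise becomes a true positive. If only adjudicated images are analysed, the readers hold opposite calls on every image, so their sensitivities must sum to 100%, and likewise their specificities.

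The arbiter is also sent the same photograph. The resulting standard is a third image reading, whereas the diagnostic criteria in 2.2 also require corresponding visual field defects.

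**Working it through.** **The plan's own figures.** The protocol gives no sample size or expected accuracy for the reader comparison. Its main calculation (6,283 per arm; × 1.20 = 7,540; ÷ 0.80 = 9,425) reproduces and has no bearing here. I use 7,540 and 3.54% (section 2.5) only to set a scale.

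**Assumed, not in the protocol.** True sensitivity/specificity: physician 75%/95%, AI 85%/93%. Two error patterns:
- Shared errors: both readers miss 10% of cases, and both raise a false alarm in 2% of non-cases.
- Independent errors: both miss 0.25 × 0.15 = 3.75% of cases; both false-positive in 0.05 × 0.07 = 0.35% of non-cases.

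Cases: 7,540 × 0.0354 = 266.9. Non-cases: 7,273.1.

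| | Shared errors | Independent errors |
|---|---|---|
| Cases, both positive | 186.8 | 170.2 |
| Cases, physician only | 13.3 | 30.0 |
| Cases, AI only | 40.0 | 56.7 |
| Cases, both miss | 26.7 | 10.0 |
| Non-cases, both positive | 145.5 | 25.5 |

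**(1) Agreement taken as truth, perfect arbiter.** Apparent positives R = both-positive cases + both-positive non-cases + discordant cases. A reader's apparent sensitivity = (both-positive cases + both-positive non-cases + cases only that reader found) / R.
- Shared errors: R = 385.7. Physician (186.8 + 145.5 + 13.3)/385.7 = 89.6%; AI (186.8 + 145.5 + 40.0)/385.7 = 96.5%. Inflation is 14.6 and 11.5 points, and the true 10-point gap becomes 6.9.
- Shared errors, specificity: apparent negatives are 7,540 − 385.7 = 7,154.3. Physician-only false positives are 3% of non-cases (218.2), giving 1 − 218.2/7,154.3 = 97.0%. AI-only are 5% (363.7), giving 94.9%.
- Independent errors: R = 282.4. Physician 79.9%, AI 89.4%. Inflation is 4.9 and 4.4 points; gap 9.5.

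**(2) Agreed positives verified at Tier 3, agreed negatives still taken as healthy.** Shared false alarms drop out of R.
- Shared errors: physician (186.8 + 13.3)/240.2 = 83.3%; AI (186.8 + 40.0)/240.2 = 94.4%. Inflation is 8.3 and 9.4 points; gap 11.1.
- Independent errors: 0.75/0.9625 = 77.9% and 0.85/0.9625 = 88.3%. Inflation is 2.9 and 3.3 points; gap 10.4.

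**(3) Discordant images only.** With shared errors, physician 13.3/(13.3 + 40.0) = 25% and AI 75%. The sum is 100% by construction.

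**(4) Agreement as truth, arbiter 85% accurate.** Of the discordant non-cases, 15% are now called glaucoma.
- Shared errors: 80.9% and 90.5% (+5.9 and +5.5 points).
- Independent errors: 69.2% and 80.6% (−5.8 and −4.4 points).

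**(5) Tier 3 for screen-positives plus the 10% recall weighted by 1/0.10.** The true values are recovered in expectation.

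**Direction.** With a correct arbiter and agreement taken as truth, apparent sensitivity and specificity never fell below the true values in 200,000 random tables, and the sign of the reader difference never flipped. The sensitivity difference depends only on the discordant cases; its size changes because the denominator does.

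**The case against.** The strongest reply is that the adjudication text describes a clinical workflow and quality control, not an analysis. No sentence says that agreed readings will be scored as correct. Section 2.6 defines sensitivity and specificity against a comprehensive reference examination (worded for the screening protocol), and the reader comparison that follows is set per participant. Section 2.2 already provides an independent examination for everyone entering Tier 3 and for a random tenth of screen-negatives. On this view the sponsor may always have meant to use it, and an analysis plan not shown may say so.

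Much of this stands. A reader might infer that the protocol has no independent standard at all, that every shared error will be counted as correct, or that both readers' accuracy is bound to be overstated. The documents support none of these. The examination exists, the scoring of agreed images is left open, and scenario 4 shows that an imperfect arbiter can push the error either way.

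The illustration has its own limits. AI reading is described within Tier 2, so the photographed group may be smaller and richer in cases than a whole arm. At an assumed 10% prevalence with the shared-error pattern, agreement as truth gives 86.1% and 95.4%, a gap of 9.3 points, so the shrinkage nearly disappears although the inflation does not.

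The reply does not dispose of the point. The protocol does more than omit a detail: it twice attaches the label of reference or gold standard to a reading of discordant images, and it assigns the verified and weighted data to something else.

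**Conclusion.** The concern holds in a conditional form. The only standard that the protocol ties to physician-versus-AI reading is unsuitable for estimating either reader's accuracy, and the suitable one is not linked to that comparison. If agreement is taken as truth and the arbiter is accurate, both readers' sensitivity and specificity are biased upward. For sensitivity this is about 3 to 15 points at the assumed true values of 75% and 85%; the range reflects how far errors are shared and whether agreed positives are verified at Tier 3. A correct arbiter preserves which reader appears better but not by how much. The figures rest on assumed accuracies and error patterns, none from the protocol.

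The consequence is confined to a secondary outcome. It would be tempting to extend it to the detection rate or to the sensitivity and specificity of the screening strategies. The documents do not support that, because those rest on the reference examination (or, for detection in the control arm, on medical records). The point deserves correction before reader data are analysed, since a reference chosen afterwards would be open to challenge.

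**What to change.** - **In 2.2, 2.6 and 2.9,** state that the reference for the physician-versus-AI comparison is the Tier 3 panel diagnosis described in 2.2.
- **Define the population** as participants whose fundus photograph was read by both physician and AI. Use all screen-positives among them plus the randomly recalled screen-negatives who were photographed, weighted by the sampling fraction. The restriction matters because Table 1 gives the tiered arm's non-high-risk group no photograph, so recalling them says nothing about reading accuracy.
- **In 2.2 and 2.7 (item 3),** keep specialist arbitration only for settling the screening result, and drop the labels reference standard and gold standard for it.

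**Cost.** This is a wording change; the examinations are already planned. Reported accuracies will probably look lower, and confidence intervals will be wider. In the illustration, a 10% recall would contain on average about 1.0 to 2.7 of the 10.0 to 26.7 shared misses (if all were screen-negative), each carrying a weight of 10. That imprecision is real and should be reported.

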This screening tool will underpin a proposed three-tiered strategy for glaucoma screening. Tier 1 Screening (Primary Screening): The pre-designed risk assessment questionnaire is administered within the community to identify high-risk individuals. Tier 2 Screening (Secondary Screening): These high-risk individuals undergo a combination of screening tests, including visual acuity, IOP measurement, fundus photography, and ocular optical biometry, which will be conducted at community healthcare or primary care centers. This stage is augmented by AI-assisted image interpretation to identify subjects suspected of having glaucoma. Tier 3 Screening (Tertiary Screening): A definitive diagnosis of glaucoma is established within the ophthalmology department of a tertiary hospital.

In the Tier 2 screening stage, fundus photographs will be interpreted using the Airdoc glaucoma-specific AI automatic screening system, which is built on a deep convolutional neural network algorithm employing an integrated multi-task learning architecture for simultaneous segmentation and classification. Standardized and traceable glaucoma grading decision rules have been established and fully integrated into the screening workflow. The system automatically performs image preprocessing, precise optic disc detection, quantitative analysis of optic disc morphology, segmentation of the optic cup and retinal nerve fiber layer defect (RNFLD) regions, and identification of glaucomatous lesions including localized RNFLD, diffuse RNFLD, optic disc hemorrhage, and optic cup notching. Moreover, it also calculates horizontal and vertical cup-to-disc ratios, ultimately generating a quantitative glaucoma risk score and a graded recommendation.

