### Follow-ups and outcome variables

2.6

Commencing at study initiation, participants will be prospectively followed up annually for a minimum of 6 years. Data will be collected yearly through IOP measurements, fundus photography, and follow-up questionnaires (Table 1). For patients with suspected or confirmed glaucoma, additional data will be collected including ocular optical biometry, RNFL thickness, and automated perimetry. Long-term follow-ups will track annual incidence and blindness rates of glaucoma, and quality of life among glaucoma patients.

**Table 1 tab1:** Follow-up schedule.

Groups		Visit number	0	1	2	3	4	5	6
		Visit time (year)	Baseline	1	2	3	4	5	6
No screening group		Questionnaire	×	×	×	×	×	×	×
Routine screening group		Questionnaire	×	×	×	×	×	×	×
		Intraocular pressure	×			×			×
		Fundus photography	×			×			×
Tiered screening group	High-risk population	Questionnaire	×	×	×	×	×	×	×
		Intraocular pressure	×	×	×	×	×	×	×
		Fundus photography	×	×	×	×	×	×	×
		Glaucoma specialist examination	Performed according to the screening results						
	Non-high-risk population	Questionnaire	×	×	×	×	×	×	×
		Intraocular pressure							
		Fundus photography							

All primary outcome measures will be analyzed on a per-participant (per-person) basis. The main endpoint of this study is glaucoma detection rate of the screening protocol, with sensitivity and specificity of the screening included as additional primary outcome measures. Glaucoma detection rate is defined as the proportion of participants in each arm with a final confirmed diagnosis of glaucoma in at least one eye, as determined by the reference standard examination in the screening arms or by passive case-finding through medical records in the control arm. Sensitivity is defined as the proportion of participants with confirmed glaucoma in at least one eye (as determined by the reference standard comprehensive ophthalmic examination) who are correctly identified by the screening protocol. Specificity is defined as the proportion of participants with no glaucoma in either eye who are correctly classified as negative by the screening protocol.

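### The reference diagnosis is made from the full clinical record with no stated masking to the screening result or AI output, so sensitivity, and possibly detection, is at risk of review bias

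*Protocol article*

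**What the plan says.** Section 2.2 (Study design) describes the reference standard. After perimetry, OCT and gonioscopy at Tier 3, "The final diagnosis will be made independently by two glaucoma specialists following a comprehensive review of all clinical data". The criterion is a clinical judgement tied to a functional test: "namely the presence of characteristic glaucomatous optic neuropathy with corresponding visual field defects". If the two readers differ, a more senior third one decides.

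The plan also deals with partial verification of those who screen negative: "a random sample of 10% of participants who are screen-negative will also be recalled to undergo the same reference standard examination". The accuracy estimates are then computed with weights for the sampling fraction.

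The same section says that the AI system reads the fundus photographs before Tier 3, "ultimately generating a quantitative glaucoma risk score and a graded recommendation".

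Section 2.6 rests the primary outcomes on this diagnosis. Sensitivity and specificity are defined against the reference examination, and detection is counted "as determined by the reference standard examination in the screening arms or by passive case-finding through medical records in the control arm".

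Section 2.7, item (4), describes the definitive perimetry and RNFL tests "with all results being evaluated and confirmed by a glaucoma specialist whose judgment constitutes the gold standard".

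No section says what the specialists are not shown.

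**The concern.** The screening pathway is the index test, and the specialists' diagnosis is the standard against which it is judged. If the specialists know the screening outcome, they can be drawn towards it: borderline screen-positives tend to be confirmed and borderline recalled screen-negatives tend to be cleared. Both errors raise apparent agreement between test and standard. The word describing the two specialists as independent separates them from each other, not from the index test.

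The plan guards against partial verification through the 10% recall. It does not stop the specialists from knowing that a person was recalled as a negative. Each recalled negative stands for about ten people, so a few altered diagnoses in that sample carry weight in the sensitivity estimate.

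At stake are sensitivity in both screening arms and, through extra confirmations among screen-positives, the detection rate, which is the main endpoint.

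**Working it through.** **The plan's own figures (section 2.5).** Two proportions, 3.54% and 4.54%, two-sided alpha 0.05, power 0.80, with continuity correction: 6,283 per arm, as stated. DEFF = 1 + (40 − 1) × 0.005 = 1.195, rounded to 1.20. 6,283 × 1.20 = 7,540. 7,540 / 0.80 = 9,425. 9,425 × 3 = 28,275. The chain reproduces and this point does not affect it. I use 7,540 as the number followed up per arm.

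**Assumptions not in the documents.** The article gives no expected sensitivity, specificity, screen-positive rate or misclassification rate. I take 3.54% as the true prevalence and treat the count as one cross-section. Everything below is illustration.

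**Check 1: effect through the 10% recall.**
- Cases per arm: 7,540 × 0.0354 = 266.9.
- True sensitivity 0.80: detected 0.80 × 266.9 = 213.5; missed 53.4; in the 10% sample 5.3.
- Wrongly clearing k sampled cases removes 10k weighted missed cases, so estimated sensitivity = 213.5 / (266.9 − 10k).
- k = 1: 213.5 / 256.9 = 0.831. k = 2: 213.5 / 246.9 = 0.865.
- True sensitivity 0.70: detected 186.8; missed 80.1; in the sample 8.0. k = 1: 186.8 / 256.9 = 0.727. k = 2: 186.8 / 246.9 = 0.757.

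**Check 2: both errors together.** Let u be the share of true cases among screen-negatives that are cleared, and v the share of non-cases among screen-positives that are called glaucoma. With true specificity 0.90:
- apparent sensitivity = (TP + v·FP) / (TP + v·FP + (1 − u)·FN)
- apparent specificity = (TN + u·FN) / (TN + u·FN + (1 − v)·FP)

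| True sensitivity | u = 0.10, v = 0.02 | u = 0.20, v = 0.05 |
|---|---|---|
| 0.60 | 0.645 | 0.697 |
| 0.70 | 0.736 | 0.777 |
| 0.80 | 0.826 | 0.854 |

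For example, at 0.70 with u = 0.20 and v = 0.05, in proportions of the arm: TP = 0.0248, FN = 0.0106, FP = 0.0965. Sensitivity = (0.0248 + 0.0048) / (0.0248 + 0.0048 + 0.0085) = 0.777. Specificity moves from 0.900 to 0.905. Detection among screen-positives moves from 2.48% to 2.96%. In the larger scenario the inflation of sensitivity is about 0.05 to 0.10 over this range; that of specificity is about 0.005.

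**Check 3: the arm comparison, only if the error differs by arm.** The effective size is 7,540 / 1.195 = 6,310 per arm. With no true difference, a false gap of 0.25 points would give about 11% rejection and 0.5 points about 31%, against a design difference of 1 point. Error of the same size in both arms produces no such gap.

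**Does the text show that it differs?** Section 2.2 places AI reading in Tier 2, which belongs to the tiered arm, and section 2.4 describes the routine arm as IOP plus fundus photography. But the later account of the workflow in section 2.2 puts all fundus photographs through both physician and AI reading, and section 2.7, item (3), repeats this without limiting it to an arm. Table 1 schedules a questionnaire at every visit in all three groups. The text is ambiguous and does not establish different dossiers.

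**The case against.** The strongest reply has four parts.

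- **It may be only a silence.** The sentence before the rule names perimetry, OCT and gonioscopy, so the record could mean the Tier 3 work-up, and a condensed article may leave masking to the full protocol. This stands in part. A reader might infer that the specialists see arm, questionnaire class and AI score. The article lists no contents, so that is not shown, and allocation is hardly clinical data. But the rule is stated, it is unrestricted, and Tier 2 measurements and readings are clinical data on any ordinary reading. The wording itself opens the record.
- **The criterion limits discretion.** A matching field defect, two readers and a third for disputes all constrain the diagnosis. This stands. It is why the outcomes can be called at risk of bias but not biased.
- **The numbers are assumed.** Clearing one or two of 5.3 cases means dismissing 19% or 38% of true cases in the recall (12% or 25% at sensitivity 70%). No document figure supports such rates. This stands, so the arithmetic shows leverage only.
- **The two descriptions of the assessor can coexist.** A reader might infer a contradiction between the two-plus-one panel in section 2.2 and the single specialist in section 2.7. Item (4) concerns who confirms the perimetry and RNFL results, while section 2.2 concerns the final diagnosis. This stands: the gold-standard wording needs aligning and is not a clear conflict.

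**Conclusion.** The point holds as a risk created by a stated rule. The specialists who set the reference standard are given the clinical record without restriction, and nothing in the article keeps the screening result or AI output from them.

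- **Sensitivity** is at risk of upward bias in both screening arms. On the assumed rates, one wrongly cleared recall moves 80% to about 83% or 70% to about 73%. The true size is unknown.
- **Specificity** is barely affected, by about 0.005 in the larger scenario.
- **Detection** in the screening arms is at risk through extra confirmations. A reader might infer that this favours the tiered arm. The documents do not support that, because AI reading and questionnaires are not clearly confined to it. Tiered versus routine is affected only if the error differs by arm.
- **Control-arm detection** comes from medical records, so this mechanism does not reach it.

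**What to change.** In section 2.2, replace the open-ended reference to the clinical record with one standard dossier for every verified participant, whether screen-positive or recalled: perimetry, OCT, gonioscopy, IOP, unannotated disc images and relevant medical history.

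As far as practicable, withhold the arm, the screen result, the Tier 2 physician and AI readings, the AI score and the questionnaire risk class. Present recalled screen-negatives mixed with screen-positives, and apply the same rule to the third expert.

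In section 2.7, item (4), name the two-plus-one panel of section 2.2 as the gold standard for the final diagnosis.

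The cost is minor data handling to prepare the masked dossiers. There are two limits to state in the protocol. Masking may be incomplete if a specialist also examines the participant. IOP and disc images remain shared with the screening test, so some incorporation remains and should be acknowledged. The change is best made before diagnoses accrue; later repair would need masked re-reading.
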